## Abstract

**Background:**

Postoperative delirium (POD) is a frequent and serious complication in older surgical patients, characterized by acute cognitive dysfunction and fluctuating levels of consciousness. POD is associated with prolonged hospitalization, long-term cognitive decline, reduced quality of life, and increased mortality. Despite its clinical relevance, the underlying pathophysiological mechanisms remain poorly understood, and reliable biomarkers for early prediction and prevention are lacking.

**Objective:**

The CONFUSED study aims to identify molecular and clinical predictors of POD by integrating clinical data with proteomic, transcriptomic, and epigenetic analyses. The primary objective is to develop predictive models for POD using multimodal data. Secondary objectives include the identification of delirium-associated genes, proteins, and epigenetic signatures, as well as the exploration of patient subgroups at increased risk for POD.

**Methods:**

CONFUSED is a prospective observational cohort study conducted at a German university hospital. Adult patients undergoing major surgery under general anesthesia will be enrolled until 100 cases of POD have been observed, which is expected to require a total sample size of approximately 200 to 300 patients. Blood samples are collected at 4 predefined time points: before premedication, immediately after surgery, and on postoperative days 2 and 5. Samples undergo comprehensive proteomic profiling, transcriptomic analysis using RNA microarrays, DNA methylation analysis, and genotyping of selected polymorphisms. Clinical data, including demographics, comorbidities, perioperative variables, medications, and delirium assessments using the Confusion Assessment Method (CAM) and CAM for the intensive care unit, are systematically recorded. Statistical analyses include univariate and multivariate methods, as well as machine learning approaches such as random forests and support vector machines, to identify relevant biomarkers and develop predictive models. The study protocol follows STROBE (Strengthening the Reporting of Observational Studies in Epidemiology) and TRIPOD (Transparent Reporting of a Multivariable Prediction Model for Individual Prognosis or Diagnosis) guidelines and was approved by the responsible ethics committees.

**Results:**

The study was registered in the German Clinical Trials Register (DRKS00033854) on March 18, 2024. Recruitment started in January 2024 and is ongoing at the time of manuscript submission. As of now, 135 patients have been enrolled. Sample collection and laboratory analyses are ongoing. Data analysis began in January 2026, with first results anticipated in July 2026. Final data lock is anticipated after the completion of recruitment.

**Conclusions:**

By integrating multimodal molecular data with clinical parameters and applying advanced machine learning techniques, the CONFUSED study aims to improve the prediction and understanding of POD. The results are expected to support the development of personalized preventive strategies and contribute to improved perioperative care for patients at risk of POD.

## Introduction

Delirium is a common postoperative complication, particularly in patients above the age of 65 years, and its causes are still largely unexplored [1]. Nevertheless, the effects of delirium are very serious for patients and, in some cases, can even drastically affect quality of life and even life expectancy. The incidence of postoperative delirium (POD) in older patients is 5% to 10% on average but can be higher in high-risk procedures such as total joint arthroplasty [2]. POD is therefore a frequent and life-threatening complication. At the center of this clinical picture is a functional disorder of the brain. Patients are affected symptomatically by disorientation, restlessness, hallucinations, or anxiety [3]. Despite these impressive and often serious symptoms, POD is often recognized late, and successful intervention is delayed [4]. However, it should be noted that the more time elapses before the diagnosis is made, the higher the probability of a severe and complicated course of POD. POD is associated with prolonged hospital stays, extended ventilation times, increased care requirements, and higher mortality rates [5]. Recovery from POD has considerable intraindividual variability, ranging from hours to months, and can present as a hypoactive, hyperactive, or mixed subtype, characterized by symptoms such as apathy, confusion, agitation, delusions, and signs of sympathetic arousal [6]. The pathophysiology of POD is not yet fully understood, but it is hypothesized to be related to acute disruptions in neurotransmitter levels and neuroinflammation [1]. Risk factors for POD include preoperative impaired cognitive and general health status, frailty, medical comorbidities such as hypotension and hypoxia, and exposure to psychoactive drugs [7]. Postoperative neuroinflammation, which is a major contributor to the development and progression of POD, can be exacerbated by complications such as infections, pulmonary issues, and hypoxemia [8]. The use of certain anesthetics has also been linked to long-term alterations in brain morphology and function, particularly at the extremes of age [9,10]. It is known from previous studies that the plasma levels of neuron-specific enolase and S-100 β protein may correlate with POD [11]. However, there are currently no valid laboratory tests for diagnosis. Furthermore, apart from an avoidance strategy for possible triggering drugs, there are only a few effective preventive and therapeutic approaches [3,12,13]. Existing models rely on clinical variables or single biomarkers. Our study integrates multiomics with advanced machine learning (ML) to explore novel predictive signatures and underlying biological mechanisms.

The aim of this study is to develop a prediction tool for POD in patients undergoing surgery. The study will address the following main objectives:

Identification of significant differentially expressed genes and proteins in blood samples through proteomic analyses and RNA microarrays as the basis for the development of predictive modelsCollection and integration of clinical dataDevelopment of a delirium prediction model based on ML, combining clinical data with data from proteomics and genetics

Following these preliminary tasks, the developed predictive models will be validated in a new independent patient cohort. These efforts will extend beyond the planned initial funding. It is expected that the results of the overall study will contribute to the development of new diagnostic tests and clinical decision tools.

## Methods

This study is a prospective observational study conducted in the Department of Anesthesia of a German university hospital. The protocol follows the STROBE (Strengthening the Reporting of Observational Studies in Epidemiology) and TRIPOD (Transparent Reporting of a Multivariable Prediction Model for Individual Prognosis or Diagnosis) guidelines.

### Ethical Considerations

The study was reviewed and approved by the Ethics Committee of the Medical Faculty of Ruhr University Bochum (approval number 23‐7794) and the Ethics Committee of Westfalen-Lippe (approval number 2024‐082-f-S). All participants will be recruited from the anesthesia outpatient clinic and provided written informed consent prior to participation. The study will be conducted in accordance with the Declaration of Helsinki and relevant local regulations. Participant privacy and data confidentiality will be strictly maintained throughout all stages of data collection, analysis, and reporting. No financial compensation will be provided to participants.

### Patient Recruitment

Patients are recruited after registration in the anesthesia outpatient clinic of the Department of Anesthesiology, Intensive Care Medicine, and Pain Therapy. All patients presenting to the preanesthesia clinic are screened for eligibility to participate in the study. Eligible patients undergo medium to major surgical procedures under general anesthesia. This approach ensures that recruitment is as efficient as possible, allowing us to reach a sufficient number of patients with delirium in a timely manner. Patients are recruited based on the inclusion criteria and the absence of exclusion criteria in the preoperative assessment clinic. The study will be concluded once 100 patients with delirium have been enrolled. Patients without delirium form the control cohort. The inclusion and exclusion criteria are provided in Textbox 1.

Textbox 1.Inclusion and exclusion criteria of the study.Inclusion criteria:Age ≥75 yearsDelirium Risk Assessment Score ≥5Medium to major surgical procedures under general anesthesia, including:Endoprosthetic procedures (hip and knee joint)Traumatological procedures for femoral neck fracturesSpinal disc surgeryVisceral surgery including cholecystectomyExclusion criteria:Age <75 yearsDelirium Risk Assessment Score <5Existing anticholinergic medicationIntracerebral interventionPreexisting severe dementiaPharmacological immunosuppressionChronic skin diseasesPatient refusalPrevious participation in this study

### Sample Size Considerations

The study is designed as an exploratory, hypothesis-generating investigation with a focus on identifying biomarkers and predictive signatures associated with POD. Rather than relying solely on a fixed total sample size, the study aims to include a sufficient number of patients with incident POD to enable meaningful exploratory analyses.

Specifically, the target is to observe 100 patients who develop POD. Based on historical incidence rates of POD in older surgical patients, including data from a systematic review of 3533 patients across 19 cohort studies [14], the pooled incidence of POD is estimated at approximately 24% (72/300) overall, with variation depending on the type of surgery (mixed noncardiac 23%, orthopedic 27%, and tumor 19%). Given this expected incidence, it is anticipated that approximately 200 to 300 patients will need to be enrolled to achieve the target number of POD cases. Recruitment will therefore continue until the required number of POD cases is reached.

We acknowledge that even with this sample size, high-dimensional omics analyses remain at risk of overfitting. To address this, feature selection, regularization techniques, and nested cross-validation will be applied to enhance the robustness and reproducibility of the findings. As such, the study is explicitly designed as an initial exploratory investigation, and any identified biomarker signatures or predictive models will require validation in larger, independent cohorts.

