## Results

### Overview

The study was registered in the German Clinical Trials Register (DRKS00033854) on March 18, 2024. Patient recruitment commenced in January 2024 and is ongoing at the time of manuscript submission (Table 2). As of now, 135 of the approximately planned 200 to 300 patients have been enrolled, corresponding to approximately two-thirds of the target sample size. Sample collection and laboratory analyses are ongoing. Enrollment is proceeding according to the projected timeline (Table 1), and no major protocol deviations have occurred to date. The first results are expected in July 2026.

**Table 2. T2:** Timeline of the study.

Item	Details
Initial ethical approval	Approved in May 2023
Funding date	Funded in January 2023
Ethical approval amendment	Approved in March 2024
Trial registration	Registered in the German Clinical Trials Register (DRKS00033854) on March 18, 2024
Start of recruitment	Recruitment started in January 2024
End of recruitment	Recruitment is expected to be completed in December 2026
Sample size status	As of February 2026, a total of 135 participants have been enrolled
Data collection period	Data collection is planned from April 2024 to March 2027
Laboratory analyses	Laboratory analyses commenced in February 2026
Statistical analysis	Statistical analysis is scheduled to begin in July 2026
Expected publication	First results are expected to be published in Spring 2027

Biospecimen collection at all 4 predefined perioperative time points is ongoing. Sample processing, including initial proteomic and transcriptomic preparation steps, has been initiated in parallel with recruitment to ensure standardized handling and storage conditions. Comprehensive laboratory analyses are currently underway.

Data cleaning and database validation procedures are being performed continuously. Final data lock is anticipated after the completion of recruitment. Statistical analyses, including integrative multiomics evaluation and the development of predictive models, began in January 2026. First results are expected in March 2026, with dissemination through peer-reviewed publications planned thereafter.

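### At the protocol's own 24% incidence, 100 delirium cases need about 417 patients; the stated 200 to 300 would give only 48 to 72 cases

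*Protocol article*

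**What the plan says.** Sample Size Considerations fixes one design quantity, the number of cases: "the target is to observe 100 patients who develop POD". It then gives the expected incidence, saying that "the pooled incidence of POD is estimated at approximately 24% (72/300) overall", with 23% for mixed noncardiac, 27% for orthopedic and 19% for tumor surgery. The next sentence draws the enrolment forecast explicitly from that incidence: "it is anticipated that approximately 200 to 300 patients will need to be enrolled to achieve the target number of POD cases". Recruitment is to go on until the case target is met. The Abstract repeats both numbers: patients are "enrolled until 100 cases of POD have been observed, which is expected to require a total sample size of approximately 200 to 300 patients".

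Results (Overview) reports 135 patients enrolled, "corresponding to approximately two-thirds of the target sample size", and describes enrolment as on schedule. Table 2 dates that count to February 2026 and adds "Recruitment is expected to be completed in December 2026". Trial Status gives November 2026 instead, and 15 January 2024 as the date of the first patient. No count of POD cases so far is given.

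**The concern.** The forecast of 200 to 300 patients does not follow from the incidence it is said to rest on. The fraction printed beside the 24% already shows this, since it puts 72 cases, not 100, in 300 patients.

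The number of cases limits the precision of every biomarker comparison and every prediction model in the study, and Strengths and Limitations calls the planned sample size sufficient for exploratory analysis. If the enrolment figure and end date are followed, the study closes well short of 100 cases. If the case rule is followed, it runs far beyond the stated end. The document does not say which governs. The progress statement hides the gap because it counts patients against the lower end of the range, whereas the target is in cases.

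**Working it through.** **Inputs.** From Sample Size Considerations: target 100 cases; incidence 24% overall, 19% to 27% by type of surgery; stated enrolment 200 to 300. From Results and Trial Status: first patient 15 January 2024; 135 enrolled as of February 2026; recruitment to end in November or December 2026.

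**1. Can the stated enrolment be reproduced?** Patients needed = 100 / incidence, rounded up.

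| Incidence | Patients for 100 cases | Expected cases in 200 | Expected cases in 300 |
|---|---|---|---|
| 27% | 371 | 54 | 81 |
| 24% | 417 | 48 | 72 |
| 23% | 435 | 46 | 69 |
| 19% | 527 | 38 | 57 |

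No cited incidence gives 300 or fewer. An allowance for dropout would only raise the number.

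**2. What incidence would make it right?** 100/300 = 33% and 100/200 = 50%. Neither figure, nor anything between, appears in the document.

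**3. Could chance bridge the gap?** The exact binomial probability of at least 100 cases among 300 patients is 0.00016 at 24% and 0.009 at 27%. Among 200 patients at 24% it is about 2 × 10⁻¹⁵. For an 80% chance of at least 100 cases at 24%, about 447 patients are needed.

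**4. Progress.** 135/200 = 67.5%, 135/300 = 45%, 135/417 = 32%. Two-thirds is right only for the bottom of the range.

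**5. End date (assumes constant accrual).** From 15 January 2024 to a point in February 2026 is 24.6 to 25.5 months, so accrual is 135/25.5 = 5.3 to 135/24.6 = 5.5 patients per month. From the first patient to the end of November or December 2026 is 34.5 to 35.5 months. The projected total is therefore about 183 to 195 patients. At 24% that is 44 to 47 cases; over 19% to 27% it is 35 to 53. Having 100 cases by then would need an incidence of 51% to 55%. The remaining 417 − 135 = 282 patients would take about 51 to 53 more months, into 2030.

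**6. Effect on precision (assumed AUC).** The document gives no expected AUC, so I assume 0.75 and show 0.70 and 0.80. Hanley–McNeil, with n₁ cases, n₀ controls, q₁ = A/(2−A) and q₂ = 2A²/(1+A):

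SE² = [A(1−A) + (n₁−1)(q₁−A²) + (n₀−1)(q₂−A²)] / (n₁n₀), and half-width = 1.96 × SE.

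| Cases/controls | AUC 0.70 | AUC 0.75 | AUC 0.80 |
|---|---|---|---|
| 100/317 | 0.063 | 0.060 | 0.055 |
| 72/228 | 0.074 | 0.070 | 0.065 |
| 45/143 | 0.093 | 0.089 | 0.083 |

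The loss from 100 to 72 cases is modest. The larger loss, at 45 cases, depends on the accrual projection in step 5.

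**The case against.** **The study is case-driven.** The enrolment figure is an approximate forecast, and the rule of continuing to 100 cases protects the planned precision. This stands in principle, and a shortfall is therefore not certain. It does not make the forecast right, and the rule cannot be squared with a 2026 end date at the reported accrual.

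**The cohort is enriched.** Patients must be at least 75 years old with a Delirium Risk Assessment Score of at least 5, so the true incidence may exceed a figure taken from older surgical patients generally. That is plausible, and it makes the projected case counts conditional. But the document derives 200 to 300 from the 24% itself and offers no rate near 33% to 50%. The only other average it gives is lower: "The incidence of postoperative delirium (POD) in older patients is 5% to 10% on average", with an unquantified remark that high-risk procedures can exceed it.

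**Accrual may have started slowly.** Table 2 dates data collection from April 2024. Counting the 135 from 1 April 2024 gives about 188 to 202 patients by the end of November or December 2026, or 45 to 48 cases at 24%. Whether enrolment just reaches 200 is therefore open; that it falls far short of 417 is not.

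**The study is exploratory.** This lowers the stakes of a wide confidence interval. It does not excuse a wrong figure for the one quantity that the design fixes.

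**Conclusion.** The concern holds. The stated enrolment is wrong on the protocol's own incidence: 417 patients are needed, not 200 to 300, and the stated range yields 48 to 72 cases, or 48% to 72% of the target. This part rests only on the document's figures. The projection of 44 to 47 cases by the end of 2026 rests on constant accrual and 24% incidence, and the AUC half-widths rest on an assumed AUC. Those parts should be read as scenarios until the observed case count is known. The point must be fixed because the case target, enrolment forecast, progress claim and end date cannot all be true as written.

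**What to change.** Make the numbers agree in the Abstract, Sample Size Considerations, Results and Trial Status by one of three routes:

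- Keep 100 cases and state about 417 patients (371 to 527 over the cited incidences), with an end date to match.
- Keep 200 to 300 patients and restate the target as about 48 to 72 cases, with the precision that gives. This changes the stopping rule as well as the forecast.
- Keep both figures and document an incidence of 33% to 50% for this enriched cohort, for example from the rate among the 135 enrolled.

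Whichever route is taken:

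- Remove the fraction 72/300 or label it as an illustration. Placed where it is, it reads as a result of a review of 3533 patients.
- Replace the two-thirds statement with the number of POD cases to date against the case target.
- Give one end of recruitment in place of November and December 2026, with the number of cases expected by then, and say whether the date or the case count governs.

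The second and third routes need no patients beyond those planned, though under the second the stated yield and precision become less favourable. The first means more patients, assays and time than the document now forecasts, although the existing stopping rule already implies them at 24%.

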### Patient Information and Consent

Participation in the study is voluntary. Prior to the start of the study, patients are informed both verbally and in writing about the nature and scope of the planned investigation, with particular emphasis on the potential health benefits and possible risks. Informed consent or assent will be obtained by the principal investigator or a qualified, trained study physician through a face-to-face discussion with the participant or authorized proxy, using the approved information sheet and consent form, ensuring adequate time for questions and written documentation of consent. Consent is documented by the patient’s signature on the consent form. This consent can be withdrawn at any time without giving reasons and without negative consequences for the patient’s further medical care. It should be noted that the patients will not have any direct benefit from the study, but the knowledge gained will benefit future patients. Participants who experience harm related to trial participation will receive appropriate medical care and compensation in accordance with applicable regulations, and provisions for ancillary and posttrial care will be ensured as clinically indicated.

### Methodology

After obtaining consent, patients are enrolled in the study. The study workflow for each patient is outlined in Table 1 and illustrated in Figure 1.

**Table 1. T1:** Study timeline detailing the timing of various procedures and data collection points throughout the study for each individual patient.

Time point	Study enrollment	Baseline	Preoperative (induction)	Intraoperative	Postoperative (recovery room)	Day 1	Day 2	Day 3	Day 4	Day 5	Hospital discharge	30-day follow-up	90-day follow-up
Study enrollment													
Screening for inclusion and exclusion criteria	✓												
Informed consent	✓												
Measurements													
Blood collection			✓		✓		✓		✓				
Microarray analysis of whole blood RNA		✓			✓								
Epigenetic analysis of whole blood DNA		✓			✓								
Genotyping of whole blood DNA		✓											
Serum/plasma storage		✓	✓	✓	✓		✓		✓				
ELISA^a^ from serum samples		✓	✓	✓	✓		✓		✓				
Isolation of neutrophils*,* PBMCs^b^, and macrophages		✓	✓	✓	✓		✓		✓				
Proteomic analyses		✓	✓	✓	✓		✓		✓				
AChE^c^ measurement		✓	✓	✓	✓	✓	✓	✓	✓	✓			
Clinical data collection													
Demographic and medical baseline data		✓											
Surgery-specific data				✓									
Complete digital anesthesia documentation			✓	✓	✓								
Intraoperative EEG^d^ monitoring				✓									
All clinical parameters		✓	✓	✓	✓	✓	✓	✓	✓	✓	✓		
Complete progress documentation		✓	✓	✓	✓	✓	✓	✓	✓	✓	✓		
Delirium screening (CAM^e^ or CAM-ICU^f^)			✓	✓	✓	✓	✓	✓	✓	✓	✓		
Neuropsychological status (RBANS^g^)											✓	✓	✓
Health-related quality of life (SF-36^h^)											✓	✓	✓
Mortality											✓	✓	✓

a ELISA: enzyme-linked immunosorbent assay.

b PBMSs: peripheral blood mononuclear cells.

c AChE: acetylcholinesterase.

d EEG: electroencephalogram.

e CAM: Confusion Assessment Method.

f CAM-ICU: Confusion Assessment Method for the intensive care unit.

g RBANS: Repeatable Battery for the Assessment of Neuropsychological Status.

h SF-36: 36-item Short-Form Health Survey.

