### Blood Sampling and Analysis

In addition, 20 mL of venous whole blood will be collected in ethylenediaminetetraacetic acid, serum, RNA exact, and DNA exact tubes (Sarstedt) at 4 points in time: during premedication, immediately postoperatively, on the second postoperative day, and on the fifth postoperative day. Serum and plasma samples, proteins, DNA, and RNA will be extracted from these whole blood samples. Furthermore, specific cell fractions such as neutrophils, macrophages, and peripheral blood mononuclear cells will be isolated. Proteins will be isolated from these cell samples and, together with plasma, subjected to the proteomic analysis using mass spectrometry to identify potentially significant proteins. Concurrently, an analysis of candidate genes, such as ACHE, BCHE, CHRNA7, chemokines, and cytokines, will be conducted to investigate methylation processes associated with the occurrence of POD. For methylation analysis, DNA samples are subjected to bisulfite conversion, and methylation will be quantified using quantitative polymerase chain reaction with specific primers [17]. The activity of acetylcholinesterase and butyrylcholinesterase will be assessed using ELISA (enzyme-linked immunosorbent assay).

In addition, an in silico analysis of the identified target genes will be performed to identify potential polymorphisms. Polymorphisms that appear potentially relevant will be genotyped in the entire patient cohort using the TaqMan Assay (TaqMan SNP Genotyping Assays; Thermo Fisher) [18,19]. In the final step, the identified genes and proteins will be quantified together with known inflammatory markers (tumor necrosis factor-α, interleukin-6 [IL-6], and interleukin-10) from serum samples using ELISA or the LegendPlex assay (BioLegend) [20]. The blood plasma obtained during cell isolation will also be used for measuring tumor necrosis factor-α and other cytokines (IL-6, interleukin-10, etc) via ELISA. In addition, neuron-specific enolase and S-100 β protein levels will be determined from the remaining blood preoperatively and 48 hours and 5 days postoperatively. The remaining DNA, RNA, and plasma samples will be stored at −20 °C and −80 °C to ensure the possibility of repeat measurements in case of technical errors. The samples will also be preserved for further validation of significant proteins from the proteomic analysis using ELISA and to investigate their genetic basis (polymorphisms and DNA methylation).

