### Integrative Data Analysis and AI Model Development

This section describes the planned integration and analysis of clinical and multiomics data for the exploratory investigation of potential predictors of POD. Data will be analyzed both independently and in combination with a focus on patient groups with and without POD. Prior to analysis, clinical datasets will be preprocessed; for example, variables with more than 30% missingness will be discarded, whereas remaining gaps will be imputed, where applicable, when missing at random, using multiple imputation by chained equations or other suitable methods. Clinical continuous variables will be centered and scaled to *z* scores, and categorical variables will be one-hot encoded. In proteomics, the analysis will involve deriving accurate quantitative protein data from peptide data, particularly by improving the utilization of shared peptides found in multiple proteins.

Univariate analyses, such as *t* tests and ANOVA (with adjustments for multiple comparisons), will be applied to identify candidate features, which may subsequently be subjected to pathway and enrichment analyses to generate mechanistic hypotheses regarding molecular processes potentially involved in POD. Multivariate techniques, including principal component analysis and clustering, will be applied to uncover latent patient phenotypes beyond a priori groupings.

The significant findings from clinical and omics data are fed into a knowledge base for targeted searches, facilitating focused investigations (targeted proteomics). The entire dataset is also analyzed using multivariate methods, including principal component analysis and clustering, to reveal latent patient phenotypes beyond a priori groupings. Supervised prediction of POD will rely on a benchmark suite of algorithms (eg, regularized logistic regression, random forests, support vector machines, and gradient-boosting methods). Model training and hyperparameter tuning will follow a nested cross-validation scheme, supplemented by a temporally separated holdout set when sufficient data are available. Discrimination and calibration will be reported with area under the receiver operating characteristic curve, area under the precision-recall curve, sensitivity, specificity, accuracy, and *F*-score. The final modeling protocol will be chosen on the basis of performance, interpretability, and clinical plausibility and can be iteratively updated as additional data accumulate.

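### Whole-blood expression and methylation are compared between POD and non-POD patients with no stated account of leukocyte composition, so a difference in cell mix may be read as delirium-associated genes or epigenetic signatures

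*Protocol article*

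**What the plan says.** The relevant statements, all in the protocol article:

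- **Material and timing.** Table 1 (Methodology) has the rows "Microarray analysis of whole blood RNA" and "Epigenetic analysis of whole blood DNA", each ticked at baseline and postoperatively in the recovery room. Blood Sampling and Analysis confirms the source: "Serum and plasma samples, proteins, DNA, and RNA will be extracted from these whole blood samples".
- **Methylation assay.** After bisulfite conversion of DNA for candidate genes (ACHE, BCHE, CHRNA7, chemokines, cytokines), "methylation will be quantified using quantitative polymerase chain reaction with specific primers".
- **Cell fractions.** From the same draws, "specific cell fractions such as neutrophils, macrophages, and peripheral blood mononuclear cells will be isolated". Their only stated use is protein: "Proteins will be isolated from these cell samples and, together with plasma, subjected to the proteomic analysis using mass spectrometry".
- **Contrast.** Patient Recruitment: "Patients without delirium form the control cohort". The comparison is POD against no POD.
- **Feature selection.** Integrative Data Analysis and AI Model Development gives univariate analyses, with examples: t "tests and ANOVA (with adjustments for multiple comparisons), will be applied to identify candidate features".

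The article names no leukocyte differential, estimate of cell proportions or composition covariate. Strengths and Limitations notes that peripheral blood may not reflect the central nervous system, but does not mention cell mix. Routine laboratory values are exported (Clinical Data Collection and Processing), without saying whether a differential count at the study draws is among them.

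**The concern.** A whole-blood expression or methylation value is a weighted mean over cell types, with the cell proportions as weights. If two groups differ in those proportions, the value differs between them even when no cell type has changed.

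The article's own premises make such a difference plausible here. The Introduction treats neuroinflammation as a major contributor to POD and says infection can worsen it. Comparison With Prior Work links C-reactive protein and IL-6 to higher delirium risk. Textbox 1 mixes femoral neck fracture with joint replacement, disc and visceral surgery, and Sample Size Considerations gives POD incidence from 19% to 27% by type of surgery. Several candidate genes code for chemokines and cytokines.

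The identification of delirium-associated genes and epigenetic signatures is at stake. Hits go on to pathway and enrichment analysis, targeted proteomics and the choice of polymorphisms to genotype. A composition difference carried along that path would be interpreted as gene regulation. Nested cross-validation would not reveal this, because the same group difference in cell mix recurs in every fold.

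**Working it through.** The article gives no figure on this point, so there is none to reproduce. The check asks how often a locus with no within-cell change would be flagged.

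**Inputs**

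- Group sizes: 72 POD and 300 − 72 = 228 non-POD, from the 24% (72/300) in Sample Size Considerations.
- Assumed, not in the article: the locus is 20% methylated in neutrophils and 70% in other leukocytes (contrast 50 points); SD of neutrophil share 8 points; assay SD 3 points; difference in mean share between POD and non-POD 0, 2 or 4 points.

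**Model.** With neutrophil share n, bulk methylation = 20n + 70(1 − n). The spurious group difference in absolute terms is contrast × share difference:

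- 0.50 × 2 = 1 point
- 0.50 × 4 = 2 points

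**Precision**

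- SD of the bulk value = √((0.50 × 8)² + 3²) = √(16 + 9) = 5 points
- SE of the group difference = 5 × √(1/72 + 1/228) = 0.676
- Standardised shifts = 1/0.676 = 1.48 and 2/0.676 = 2.96

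**Probability of being flagged**, normal approximation, two-sided. Critical values are 1.960 at 0.05, 3.023 at 0.05/20 and 4.708 at 0.05/20,000.

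| Contrast | Share difference | 0.05 | Bonferroni, 20 loci | Bonferroni, 20,000 probes |
|---|---|---|---|---|
| 50 points | 0 | 0.05 | 0.0025 | about 0 |
| 50 points | 2 points | 0.32 | 0.06 | 0.0006 |
| 50 points | 4 points | 0.84 | 0.47 | 0.04 |
| 10 points | 2 points | 0.08 | 0.006 | about 0 |
| 10 points | 4 points | 0.16 | 0.02 | 0.0001 |

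Simulation of the 50-point case (4,000 studies per setting) gives 0.31 and 0.84 unadjusted, and 0.05 in both when neutrophil share is a covariate measured without error.

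**Second setting.** With 100 POD and 200 non-POD, contrast 30 points and the same SDs (2,000 simulated studies), unadjusted rejection at 0.05 is 5.8%, 26%, 88% and about 100% for share differences of 0, 2, 5 and 8 points. With share as a covariate it is 4.7% to 4.9% throughout. By formula, the 5-point difference gives 0.89 at 0.05, 0.57 over 20 loci and 0.06 over 20,000 probes.

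**Imperfect adjustment.** If share is estimated with reliability r, the covariate removes only a fraction r of the artefact, so (1 − r) × contrast × share difference remains. With r = 0.8 as an illustration, shifts of 1 and 2 points fall to 0.2 and 0.4 points, not to zero.

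**The case against.** The strongest reply is that this is silence in a condensed article. Trial Status says a statistical analysis plan exists, it is not shown here, and t tests and ANOVA are given as examples. A composition covariate could be specified there. That stands: one cannot conclude that no correction will be made. What the article does fix is whole blood as the material, protein as the only described use of the fractions, and a selection step described with multiplicity adjustment alone. An analysis plan can use measured composition only if it was measured at the draw.

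Four stronger readings are tempting and not supported.

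- *Any perioperative neutrophil shift will produce false hits.* The contrast is POD against non-POD, so a shift shared by both groups cancels. A change within patients between the two draws does not by itself bias that contrast. Bias needs a share that differs by POD status, and the article gives no figure for this.
- *The planned multiplicity adjustment is irrelevant.* It lowers the rates substantially, as the table shows. It raises the threshold without removing the bias, so the exposure that remains is mainly in a small candidate panel with strong lineage contrasts.
- *The prediction models are invalidated.* A composition-driven signal can be a valid predictor, and prediction is the primary objective.
- *A marker that fails adjustment should be discarded.* Cell mix may lie on the path to POD, so such a rule could drop real signals.

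The 50-point contrast is also favourable to the concern and is not tied to any named candidate gene. The article calls the study exploratory and says that mechanism and causality need further research. That limits what will be claimed, but does not correct a systematic difference.

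**Conclusion.** The point holds in conditional form. As described, the analysis cannot separate a POD versus non-POD difference in leukocyte mix from a difference in expression or methylation within cells, so composition may be reported as delirium-associated genes or epigenetic signatures.

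The size depends on inputs the article does not give. For a locus with a 50-point contrast and a share difference of 2 to 4 points, the risk is about 31% to 84% at 0.05 and about 6% to 47% after Bonferroni over 20 loci. It is 4% or less over 20,000 probes. It is 8% to 16% at 0.05 for a 10-point contrast, and nominal if the share does not differ. The consequence falls on the secondary, biological aim and the work that follows from it, much less on prediction. The remedy is inexpensive and worth adopting.

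**What to change.** For every whole-blood expression and methylation comparison, specify a second, composition-adjusted model and report it beside the unadjusted estimate.

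- **Covariate.** Use the leukocyte differential from the same draw where the routine laboratory export has it, and otherwise cell proportions estimated from the microarray. The qPCR methylation assay on candidate genes gives no such estimate, so it should borrow one of these.
- **Availability.** State whether a differential is obtained at the baseline and recovery-room draws. The article discards clinical variables with more than 30% missing values, so a differential that is only sometimes ordered could be lost under that rule. Recruitment is still open, so later patients can be covered.
- **Wording of results.** Describe hits that vanish on adjustment as composition-related, not as gene regulation. Do not make survival of adjustment a condition for keeping a marker as a predictor.

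The cost is a few covariates and one more column of results. There are two downsides. Adjusted effects exclude any part of the association that runs through cell mix, which is why both estimates are needed. Estimated proportions carry error, so adjustment may be incomplete and should be described that way.
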